## Abstract

**Highlights:**

**What are the main findings?**
The use of virtual reality will produce substantial kinematic data of upper limb motor performance, including reaction time, movement time, time to peak velocity and acceleration, and normalized jerk.The neural mechanisms underlying these movements, assessed via functional near-infrared spectroscopy, will provide a deeper, neurobiological context for these kinematic data.

**What are the implications of the main findings?**
Multimodal methods incorporated into motor development and performance research are essential to establishing a comprehensive understanding of clinical populations with differences across multiple developmental domains.Combining kinematic data with neural biomarkers will lay the foundation for supplementing behavioral assessment methods in autism, as well as contribute to potential cognitive and motor intervention and support strategies using virtual reality.

**Abstract:**

**Background/Objectives**: In both typical and atypical development, there is growing evidence that motor development sets the stage for development in other domains. This study aims to examine the feasibility of conducting cognitive and motor research-based tasks in a virtual reality (VR) environment with concurrent neuroimaging (functional near-infrared spectroscopy, or fNIRS) in autistic children. **Methods**: During a single study visit, participants will complete research-based tasks conducted in a virtual reality environment while wearing the fNIRS apparatus. Supplementary procedures will include a range of standardized assessments and questionnaires for caregivers and their children to complete. **Anticipated Outcomes**: These methods will yield a rich combination of data -- the kinematic data associated with performance during the research-based tasks, as well as the neural correlates underlying this performance. **Conclusions**: The overarching, long-term goal of this feasibility study is to explore the interrelationships between cognitive, motor, and social development in autistic children using a variety of research methodologies. A better understanding of these relationships and their neural correlates will inform future research, assessment methods, and intervention strategies across the autism spectrum.

## 1. Introduction

Foundational research in motor development suggests that motor development is a lifelong process, with significant periods and stages occurring throughout childhood and adolescence [1]. Most fundamental patterns of movement are well-established by the age of 7—however, beyond this point, motor development remains a continuous and adaptive process. For example, school-age children between the ages of 8–12, situated within the “context-specific” period of motor development, are learning to apply basic motor execution to motor performance within more complex settings requiring cognitive and motor skills, such as sports and games [1]. However, motor development does not simply occur alongside these changes in cognition—in both typical and atypical development, there is growing evidence that motor development sets the stage for development in other domains across the lifespan [2,3,4,5,6,7,8,9,10,11,12,13]. These complex interactions between and across developmental domains throughout the lifespan are otherwise known as developmental cascades [14]. The characteristics of the physical human body, the environment in which the body is contextualized, and the interrelations between these domains as a child grows promote opportunities for exploration, learning, and, ultimately, psychological development [14]. Hence, the study of motor development beyond infancy and across a variety of neurotypes is crucial to a comprehensive understanding of human development.

These developmental cascades, particularly with regard to motor development, remain relevant well into childhood and adolescence, with their effects becoming increasingly apparent in pediatric autism research [15]. Motor differences, which are highly prevalent among autistic individuals [16,17,18], are strongly associated with impairments across other developmental domains [19]. A wealth of literature has shown cascading effects between motor development impairments in autism and language delays [20], adaptive behavior [21,22], and communication skills [23,24]. Moreover, the risk of motor impairment increases with increased impairment across other areas of development [25]. Motor development research in autism has crucial implications for assessing and supporting autistic individuals both across the lifespan and across the spectrum, who have varying support needs through multiple developmental domains.

The traditional gold-standard methods of autism diagnosis and assessment rely on behavioral characteristics, particularly related to social skills and cognitive abilities. The strengths of these assessments are vast and undeniable—they are validated scientific methodologies that are rigorously tested and acknowledged as gold-standard diagnostic measures across both clinical and scientific communities. However, as with all methodologies, limitations remain—for example, the potential for clinician error or bias [26], and a tendency towards missing the female-specific manifestations of autistic traits [27]. Furthermore, commonly used standardized assessments (e.g., Autism Diagnostic Observation Schedule, Autism Diagnostic Interview-Revised) are not intended for use among those with severe motor difficulties or intellectual impairment [26,28]. Therefore, to fully understand the relationships between motor development and other developmental domains, as well as the variability within these relationships, it is crucial to utilize a comprehensive combination of methodologies and assessments. We can gain a variety of outcomes by using a multi-modal approach—in particular, combining these traditional behavioral assessments with methods that can afford various types of physical biomarkers, such as neuroimaging [29]). For example, a combination of standardized motor assessments and movement assessment via 3D motion capture or other similar technologies during research-based tasks can fully assess a child’s motor skill and motor performance via the addition of objective kinematic data [30]. Incorporating neuroimaging can provide further biomarkers of the neural correlates underlying cognitive and motor behavior. For example, a study combining fNIRS with movement tracking during a whole-body sway synchrony task found that autistic children synced less well with a social partner and swayed with smaller amplitude compared to their non-autistic peers [31]. This reduced synchrony was accompanied by lower activity in the superior temporal sulcus and inferior frontal gyrus. Interestingly, when children swayed alone rather than with the adult, the two groups moved similarly. This suggests that the differences only emerged in socially engaged conditions [31]. A related follow-up study used a “reach-to-clean-up” task that combined kinematic and fNIRS recordings across observation, execution, and synchronization conditions in autistic and non-autistic children and found that autistic children showed a greater movement overshoot, speed, and movement segmentation both when moving alone and when synchronizing with an adult, along with reduced prefrontal and temporal activation and higher frontoparietal activation compared to the non-autistic group [32]. fNIRS has also been used with movement-based interventions; in fact, a preliminary randomized control trial used fNIRS to measure cortical activation during a drumming synchrony task before and after eight weeks of creative movement, general movement, or sedentary play interventions in children with ASD, highlighting how fNIRS can serve not only as an assessment tool but as an outcome measure [33]. Together, these studies show that combining brain imaging with movement tracking is a feasible approach for understanding motor and neural profiles of autistic youth and linking brain activity to both movement patterns and intervention response. Even so, this work has stayed narrowly focused on synchrony-based tasks or more specific tasks rather than broader everyday motor skills that are important to target in autistic children. Virtual reality (VR) is another emerging technology being used to assess motor ability [34,35] and conduct motor interventions in autistic youth [36,37]. The overarching work in this growing field, primarily intervention-based, suggests that VR-based interventions are likely feasible and effective in improving motor skills in autistic children [38]. VR has also been successfully used in interventions targeting other developmental domains in autism, such as social and communication skills [39,40,41]. Pairing a custom VR game with low-cost motion tracking, Hocking et al. had ten children and adolescents with autism complete six 20 min VR sessions over two weeks to target their gross motor skills. The authors note that manual motor difficulties in ASD predict adaptive behavior up to 12 years later, underscoring why early motor interventions matter [36]. Another pilot study offers early but meaningful insight into how children and adults with ASD use vision and proprioception in immersive VR. Notably, every participant, including those with higher support needs, readily accepted wearing the head mounted display [42]. Incorporating VR in motor assessment provides real-time measures of human movement and affords movement assessment during a diverse array of research-based VR tasks. These elements are crucial to supplementing standardized movement assessments and producing comprehensive motor profiles in clinical populations.

While much work has been conducted using these assessment techniques individually, the body of research combining these uniquely informative measures of motor, cognitive, and social development remains limited. Few studies combine VR-based tasks and interventions with standardized assessments. Many VR-based studies also lack a deeper understanding of the neural mechanisms underlying development in these domains; however, the use of neuroimaging has been a valuable supplement in previous studies involving more traditional research-based tasks [27]. In particular, neuroimaging methods that can be used during human movement and collect real-time data during task performance are of great value. A prime example is functional near-infrared spectroscopy (fNIRS), which uses near-infrared light to measure brain activity indexed via changes in blood oxygenation concentration. Although it provides a regionally limited hemodynamic measure, fNIRS offers good spatial resolution and is noninvasive, portable, suitable for research involving movement, and relatively well-tolerated by autistic children [43]. In comparison to other neuroimaging techniques such as functional magnetic resonance imaging (fMRI), fNIRS provides a measure of neural activity with superior temporal resolution in milliseconds in comparison to fMRI which lags neural activity due to the temporal resolution being restricted by hemodynamic response [44]. Although fNIRS does have restricted ability to localize brain activity while fMRI is able to provide whole brain coverage, fNIRS is more attractive to this population because of its accessibility, portability, and low cost [44]. While magnetoencephalography (MEG) provides high temporal resolution images of the brain’s electrophysiological images, it is restrictive to movement and hemodynamic changes in comparison to fNIRS [45].

While a handful of VR studies have used concurrent fNIRS as a means of understanding the neural mechanisms underpinning task performance during movement (e.g., [46,47,48]), it remains a relatively limited field, particularly in research involving neurodiverse participants. Still, work outside the motor domain hints at what this pairing could offer. Bulgarelli et al. combined wearable fNIRS with an immersive Cave Automatic Virtual environment to study social preference in preschoolers as children played with preferred versus assigned avatars, demonstrating that naturalistic combined VR-fNIRS assessment is feasible even in very young children [49]. Virtual reality and neuroimaging each have their own value—the former providing rich behavioral data within an easily manipulated environment and the latter providing biomarkers of these behaviors in the form of neural activity. The combination of these technologies is complementary, providing a comprehensive profile of behavior and its underlying biological mechanisms—the basis of what is needed to develop individualized and targeted therapies for patient populations as well as supplement and strengthen traditional assessment methods. Thus, further work is needed to assess the feasibility of combining neuroimaging with research-based tasks in a virtual reality environment, with neurodiverse individuals as the population of interest.

### Aims and Hypotheses

The goal of this proposed study is to assess motor performance—in relation to other developmental domains—in autistic children during research tasks in a VR environment with concurrent neuroimaging (fNIRS). In the current paper, we will focus on the cognitive and motor portions of this overall work. The groundwork for successfully executing this multi-modal study requires that we assess the feasibility of combining these methods and utilizing these tasks. In order to properly assess the feasibility of these proposed methods, we will use Orsmond and Cohn’s (2015) feasibility study objectives, with a strong focus on study and data collection procedures [50].

The overarching, long-term goal of this feasibility study is to explore the interrelationships between cognitive, motor, and social development in autistic children using a combination of research methodologies. A better understanding of these relationships and their neural correlates will inform our understanding of the autistic brain, enhance and diversify autism assessment methods with the use of neuroimaging, and contribute to intervention strategies involving VR across the autism spectrum. For this paper, our primary aim is to examine the feasibility of conducting cognitive and motor research-based tasks, specifically, in a VR environment with neuroimaging in autistic children, with a focus on preliminary kinematic data.

**Hypothesis** **1.**
*Our multi-modal research approach will ultimately be tolerable and feasible across the majority of participants (as measured via objective feasibility assessment questions). The objective feasibility assessment questions focus on researcher observations during the study, such as the number of participants reaching completion of all tasks and assessments, as well as the length of completion of study per participant.*

**Hypothesis** **2.**
*The majority of participants will report their VR/neuroimaging experience to be both tolerable and feasible (as measured via subjective, self-report feasibility assessment questions). The subjective feasibility assessment questions focus on the child’s feelings towards the study, such as enjoyability, and will be completed at the end of the visit.*

**Hypothesis** **3.**
*Preliminary kinematic and neural data collected using these research-based tasks will be reliable and valid measurements (i.e., preliminary examination of behavioral data suggests anticipated changes in the kinematic outcome variables of interest; acceptable signal quality is attained for neuroimaging data).*

*Measures*. This study will produce kinematic and neuroimaging data for autistic youth between the ages of 8 and 12 years old. The primary outcome measures for this study include: (1) Subjective feasibility assessment (e.g., tolerability: “Was the VR headset comfortable to wear?”, “Was the brain cap comfortable to wear?”, “Did the tasks make you tired?”, “Did you feel capable of completing these tasks?”, “Did the tasks feel too challenging?” enjoyability- “Did you enjoy these tasks?”, “Would you do them again?”, “Were the tasks engaging?”). (2) Objective feasibility assessment (e.g., How long did the entire testing battery take? How many participants completed all assessments and tasks? Did the participant exhibit any behaviors that are indicative of feeling overwhelmed, overstimulated, etc.? Did the participant experience any adverse events (e.g., cybersickness)? Preliminary behavioral and neural data—how was the data quality? Are the findings reflective of previous literature?). (3) Select neural measures (e.g., fNIRS data quality indicators, such as signal to noise ratio, and oxygenated hemoglobin concentration). (4) Select cognitive and motor behavioral measures that are specific to our research-based tasks (e.g., movement time, velocity). This combination of measures will provide a comprehensive basis for assessing the feasibility of combining neuroimaging with research-based tasks in a VR environment in autistic children.

In addition to the above primary measures, further analyses of cognitive and neural outcomes (Table S1) will be performed. Participants and their caregivers will also complete a series of questionnaires and assessments evaluating cognitive, motor, and social development (Table S2). While these outcome measures (particularly those related to social development) are not the preliminary, feasibility-based aims discussed in this paper, they are an important part of the long-term goal of this work and can be found in the Supplementary Materials for reference.

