### 2.2. Participants

This work will assess 50 autistic children and 50 non-autistic children. We anticipate having to screen a higher number of participants to accommodate ineligibility. We estimate that we will lose 10% of participants at screenings, 20% of screened participants will choose not to enroll, and 10% of participants will dropout after enrollment. Given these factors, we estimate needing to screen at least 160 participants.

All participants will be between the ages of 8 and 12 years old. This age range corresponds with the “context-specific” period of motor development, marking the transition children make from executing basic movements to incorporating these skills within more complex settings requiring cognitive and motor skills [1]. Conducting this feasibility study within this narrow yet significant age range will set the foundation for future work examining how and why autistic children might differ in their cognitive and motor abilities compared to their non-autistic peers, as well as whether these differences correspond with their engagement in complex cognitive–motor individual and group activities.

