### 2.6. Block Design and Task Details

The “Go/No-Go” paradigm is embedded within a block design, a common experimental design among fNIRS studies, which traditionally alternates task periods, or blocks, with periods of rest. There will be two experimental conditions: cognitive, and motor/cognitive–motor. The cognitive condition will consist of 6 block sets, with each task block (either go or Go/No-Go blocks) running for 24 s. Each task block will also be preceded by 3 s of brief instructions (e.g., “Press the button to pop the balloons”). Therefore, one block set (two 24 s blocks, with two sets of 3 s instructions) will total 54 s, with 6 consecutive block sets totaling 5.4 min (or 324 s). Prior to the condition, there will also be a 15 s calibration period for the headset and controllers, totaling 339 s (5.65 min) for the cognitive condition. The motor/cognitive–motor condition will consist of 12 block sets, with each task block (either go or Go/No-Go blocks) running for 24 s. Each task block will also be preceded by 3 s of brief instructions (e.g., “Press the button to pop the balloons. Be as fast and as accurate as you can.”). Therefore, one block set (two 24 s blocks, with two sets of 3 s instructions) will total 54 s, with 12 consecutive block sets totaling 10.8 min (or 648 s). Prior to the condition, there will also be a 15 s calibration period for the headset and controllers, totaling 663 s (11.05 min) for the motor/cognitive–motor condition. To mitigate possible carry-over effects between conditions, participants will be allotted up to five minutes to rest between the two conditions, and the order in which the conditions are presented will be counterbalanced across participants.

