### 3.1. fNIRS Results

The preliminary fNIRS data results, and the primary outcome of feasibility in this current paper, will be a simple assessment of the signal quality of the raw data (Table 2). Prior to data processing, this will involve a visual inspection of which channels yielded high-quality signals; i.e., channels with a visible and consistent cardiac pulsation, which is indicative of an appropriate hemodynamic response [60], and minimal visible noise due to movement or other artifacts. Then, data will be processed using Homer3 (v1.87.0) via MATLAB (R2024b), which will include pruning noisy signals, correcting the signal for motion artifact, converting the raw data to optical density, applying a bandpass filter to remove physiological noise, and converting to oxygenated hemoglobin concentration (HbO), deoxygenated hemoglobin concentration (HbR), and total hemoglobin concentration (HbT); see Figure 6 for the proposed Homer3 processing pipeline and thresholds for each respective step. These variables can then be used to infer neural activity in brain regions of interest for this task: the motor cortex, which is associated with movement, and the accessible area in the frontal cortex, which is associated with executive functions. These variables are listed in Table S1.

Once the data have been processed, we will assess feasibility based on percentage of usable channels. This will involve taking the number of channels remaining (i.e., those that have not been pruned or otherwise excluded after processing) for each participant, and dividing that number by the total number of channels (i.e., 20). Feasibility will be defined as a participant retaining 60% or more of the possible number of channels (i.e., ≥12 channels).

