Furthermore, our current research-based task design can be considered limiting in and of itself. One task with various conditions/manipulations of cognitive and motor domains certainly cannot generalize to assessing cognitive and motor development at large, particularly considering the developmental heterogeneity among autistic youth. The behavioral and neural responses elicited will be specific to the task selected, and future work using additional tasks alongside this proposed task paradigm is needed for more comprehensive developmental assessment. Standardized assessments will also be crucial to this larger, holistic understanding of developmental domains in autism. These assessments, which are further detailed in the Supplementary Materials, target cognitive (e.g., Behavior Rating inventory of Executive Function—2nd edition (BRIEF-2)), motor (e.g., Bruininks-Oseretsky Test of Motor Proficiency—3rd edition (BOT-3)—Fine Motor Portion, and social and emotional development (e.g., Social Skills Improvement System (SSIS) Rating Scales). Once the feasibility of combining neuroimaging and virtual reality in autistic youth has been established, integrating the results of these standardized measures will afford the opportunity for validating our behavioral data, as well as allow us to examine the interrelationships between clinical profiles and cognitive and motor task performance.

This feasibility study and the preliminary cognitive and motor data gathered will set the groundwork for a multitude of future studies assessing the interrelationships between cognitive, motor, and social development in autistic children. Our preliminary, simplistic research-based task design sets the stage for creating much more complex tasks across various developmental domains, with VR affording malleable, controllable, and extremely realistic environments. We hope by combining neuroimaging and virtual reality paradigms, we can use these methods in addition to traditional assessments, such as the ADOS. Furthermore, in the long-term, this work will advance multi-modal, holistic, and comprehensive autism research—viewing these relationships and their neural correlates through a multifaceted lens will inform our understanding of the autistic brain, diversify autism assessment methods, and improve intervention strategies across the autism spectrum.

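### Hypothesis 3 defines 'reliable and valid' by expected changes and signal quality, so it can be declared met with no evidence that a child's score is repeatable

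*Protocol article*

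**What the plan says.** Hypothesis 3 (Aims and Hypotheses) states that the preliminary kinematic and neural data "will be reliable and valid measurements (i.e., preliminary examination of behavioral data suggests anticipated changes in the kinematic outcome variables of interest". The second half of the same parenthesis is that "acceptable signal quality is attained for neuroimaging data". The abbreviation i.e. makes these two conditions the definition of the claim; they are not offered as examples.

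Section 3.1 gives the signal-quality half a number: "Feasibility will be defined as a participant retaining 60% or more of the possible number of channels (i.e., ≥12 channels". The kinematic half has no number, contrast or direction. Section 3 describes the feasibility outputs as descriptive and qualitative and names no test.

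The article names no reliability quantity (split-half, intraclass correlation, test-retest or measurement error) for any kinematic or neural outcome. The only reliability figure, in section 2.2, concerns administration of the ADOS-2. The Abstract describes one visit: "During a single study visit, participants will complete research-based tasks conducted in a virtual reality environment while wearing the fNIRS apparatus". Section 2.7 allows two sessions as an accommodation for fatigue or discomfort, which is not a planned retest.

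The Discussion puts validation later. Once feasibility is established, "integrating the results of these standardized measures will afford the opportunity for validating our behavioral data".

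**The concern.** Reliability concerns whether a child's score repeats and whether it separates one child from another. A change in the anticipated direction concerns the average over children. The two can come apart: a mean can move with no stable differences between children, and scores can be highly stable with no mean shift. Channel retention says how much signal survived processing, and nothing about whether the response would recur.

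As worded, the study could therefore report its measures as reliable without having looked at reliability. This matters because the stated long-term aim is to relate cognitive, motor and social development across children, and the Discussion looks ahead to linking clinical profiles with task performance. Correlations of that kind are weakened when individual scores are unreliable, whatever the group mean does.

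This goes beyond detail that an analysis plan would supply. The hypothesis itself fixes what the words mean. An analysis plan could add a reliability estimate, but Hypothesis 3 would still be met without it.

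**Working it through.** **The plan's own figure.** 60% of 20 channels is 0.60 × 20 = 12, as stated. It is a retention rule.

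**Inputs from the article.**
- Sample (section 2.2): "This work will assess 50 autistic children and 50 non-autistic children".
- Blocks (section 2.6): "The motor/cognitive–motor condition will consist of 12 block sets, with each task block (either go or Go/No-Go blocks) running for 24 s". Each block set holds one go block and one Go/No-Go block.
- Trial length (section 2.6): 3.2 s + 0.8 s = 4 s, so 24 / 4 = 6 trials per block.
- Half of the trials in a Go/No-Go block are Go trials.

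Reaches per child: motor 12 × 6 = 72; cognitive-motor 12 × 3 = 36.

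**Assumptions not in the article.** Within-child trial SD of 150 or 200 ms; a shift of 10 or 20 ms identical in every child; a two-sided paired t-test at 0.05.

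**Can the mean shift while the difference score has no reliability?** Let D be a child's cognitive-motor mean minus the motor mean.

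SE(mean D) = sqrt(SD²/72 + SD²/36) / sqrt(50)

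| Trial SD | SE | 10 ms shift detected | 20 ms shift detected |
|---|---|---|---|
| 150 ms | 30.6 / 7.07 = 4.33 ms | 62% | 99% |
| 200 ms | 40.8 / 7.07 = 5.77 ms | 40% | 92% |

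The percentages come from the noncentral t distribution; 4,000 simulated data sets per case agree to within about 1 percentage point. In every case the odd/even split-half correlation of D averaged 0.00. That is built in, because all children share one true effect. If the 10% dropout came out of the 50, leaving 45, a 20 ms shift would be detected in 99% (150 ms) or 90% (200 ms) of data sets.

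**Does this carry over to the raw measures? No.** Add an assumed between-child SD of 100 ms in reaction time, with trial SD 200 ms and 36 motor trials per half:

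split-half r = 100² / (100² + 200²/36) = 10,000 / 11,111 = 0.90; Spearman-Brown 2 × 0.90 / 1.90 = 0.95.

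The chance of detecting the shift is unchanged, because each child's own level cancels in D. The same result is therefore compatible with highly reliable raw scores and with unreliable ones. It does not tell them apart.

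**The reverse case.** With between-child SD 60 ms and trial SD 150 ms, split-half r = 3,600 / (3,600 + 625) = 0.85. With no mean shift, such data showed a significant change in the expected direction in only 2.3% of runs.

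**What could the planned data say about reliability?** Take a Spearman-Brown value of 0.70 with 50 children.
- Half-correlation: 0.70 / (2 − 0.70) = 0.538.
- Fisher z = 0.602; half-width 1.96 / sqrt(47) = 0.286.
- Limits for r: tanh(0.316) = 0.306 and tanh(0.888) = 0.710.
- Corrected back: 2 × 0.306 / 1.306 = 0.47 and 2 × 0.710 / 1.710 = 0.83.

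This is enough to separate no reliability from good reliability, but too wide to certify a value of at least 0.70 from an estimate of 0.70.

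**The case against.** **The claim is modest.** Hypothesis 3 twice calls its evidence preliminary. The article separately asks about data quality and agreement with earlier literature, and it does not present validation against standardized measures as finished. No sample size or progression rule hangs on this hypothesis. All of this stands, and it keeps the point to wording and one added analysis. It does not supply a reliability criterion.

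**Expected condition effects are evidence of validity.** This stands. A measure that responds to the task manipulation as theory predicts has some construct support, so the validity half of the definition is thin but not empty. The gap is in the reliability half.

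**The illustration rests on things the article does not state.** This also stands. The article names no paired test, no contrast and no trial SD. The 72 and 36 reaches assume a fixed 4 s per trial, whereas Table 1 has the hand reset trigger the next balloon, which would make the counts vary between children. Section 3.2 also excludes trials with tracking loss. Other counts would change the percentages but not the logic.

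**A stronger reading to avoid.** A reader might infer that the kinematic measures are unreliable, or that the study's data would fail to distinguish children. The documents do not support this. The zero reliability in the illustration is an assumption about the difference score, and the same mean result goes with a split-half correlation of 0.90 in raw reaction time under the other assumption shown.

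**Conclusion.** The point holds in a limited form. Hypothesis 3 defines reliable and valid through two criteria, and neither measures repeatability. Nothing else in the article fills that gap, so the hypothesis could be declared met with no evidence on reliability. For validity the criteria give preliminary support only, and the Discussion itself places comparison with the standardized measures after feasibility.

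The size cannot be fixed from the article. For the difference score, under the stated assumptions, a common 20 ms shift is found in over 90% of data sets at n = 50 with reliability of about 0. That shows the criterion is uninformative about reliability. It does not show that reaction time, movement time, time to peak velocity, time to peak acceleration or normalized jerk are unreliable.

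**What to change.** Choose one of two changes.

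1. **Reword.** State Hypothesis 3 as: the data will be of acceptable quality and will show the expected condition effects. Drop the claim of reliability.
2. **Keep the word reliable and support it.** For each kinematic measure in Table 2, within each group, report an odd/even-block split-half estimate, Spearman-Brown corrected, with its 95% CI. Validity should still be described as the expected condition effects.

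Under the second option, report the estimate with its interval and do not use 0.70 as a pass mark, given the interval of about 0.47 to 0.83 around it. Reliability of the cognitive-motor minus motor difference can be reported as secondary. Also report the number of usable trials per child, since trial pacing and tracking loss affect it.

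The cost is one reworded hypothesis and, under the second option, one extra analysis of blocks already planned. No further visit or data collection is needed. The stated conclusion may turn out less favourable.
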